#### Environmental data

Environmental data will be collected to assess short-term exposures, including monthly average meteorological conditions and air pollutant concentrations, matched to each patient based on their location and hospital admission period (47). Meteorological data will be obtained from the ECMWF Reanalysis v5 (ERA5) dataset, which provides monthly averaged measurements of temperature, precipitation, relative humidity, and wind speed at a spatial resolution of 0.25° × 0.25° (approximately 25 km at the equator) (48). Air pollution data will be sourced from the China High-Resolution and High-Quality Near-Surface Air Pollutants (CHAP) Dataset, which provides daily concentrations of PM2.5, PM10, ozone (O₃), nitrogen dioxide (NO₂), sulfur dioxide (SO₂), and carbon monoxide (CO) at a spatial resolution of 1 km (49–52). Green space coverage will be assessed using the NDVI, derived from NASA Moderate Resolution Imaging Spectroradiometer (MODIS) Vegetation Indices. NDVI data will be provided annually at a spatial resolution of 1 km (53).

#### Socioeconomic data

Socioeconomic data including city-level per capita, income levels, employment status, job types, education level, and living conditions will be collected during follow-up visits and sourced from the Gansu Development Yearbook, published by the Gansu Province Bureau of Statistic.

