## Methods and analysis

### Study population

This prospective cohort study, will enroll over 4000 individuals with RT-PCR-confirmedSARS-CoV-2 at baseline, hospitalized at Gansu Provincial Hospital in China from December 2022 to May 2023 (Gansu PASC dataset). Aligning with methodologies from other PASC research, we will gather comprehensive health data during the patients’ initial hospitalization due to COVID-19 (31). The data collection will include extensive hospital records from their acute COVID-19 admissions, capturing demographic information, clinical data, comorbidities, pre-existing symptoms, and other relevant health details.

The patients were from all 14 cities in Gansu Province (92°13′E-108°46′E, 32°31’N-42°57’N), with various environmental and socioeconomic backgrounds. The municipal geographic coordinates of the 14 cities are detailed as follows: Lanzhou (103°51′E, 36°3’N); Jiayuguan (98°23′E, 39°80’N); Jinchang (102°19′E, 38°52’N); Baiyin (104°14′E, 36°55’N); Tianshui (105°72′E, 34°58’N); Wuwei (102°64′E, 37°93’N); Zhangye (100°45′E, 38°92’N); Pingliang (106°66′E, 35°54’N); Jiuquan (98°49′E, 39°73’N); Qingyang (107°64′E, 35°71’N); Dingxi (104°59′E, 35°61’N); Longnan (104°96′E, 33°37’N); Linxia Hui Autonomous Prefecture (103°21′E, 35°60’N) and Gannan Zang Autonomous Prefecture (102°91′E, 34°98’N). Baseline data will be collected using hospital records, and follow-up assessments will be performed at 24-, 36-, and 48-months post-discharge via structured telephone interviews (Table 1). Exclusion criteria are limited to individuals without available contact details, those who deceased during hospitalization or follow-up, those who declined to participate, and those unreachable for follow-up assessments.

**Table 1 tab1:** Evaluation parameters at baseline and follow-up visits.

Evaluation parameter	Baseline°	Follow-Up°° (telephone interviews)		
	(Hospital admission)	Visit 1 (24 m)	Visit 2 (36 m)	Visit 3 (48 m)
Informed consent	x			
Inclusion criteria met	x			
Demographics*	x			
Environmental/socio-economic factors†	x			
Symptoms‡	x	x	x	x
Life styles¶	x	x	x	x
Vaccination information**	x			
Reinfection††		x	x	x
Recovery condition‡‡		x	x	x
Comorbidities¶¶	x			
Laboratory test results***	x			
Treatment†††	x			
Clinical outcomes	x			
Medical management‡‡‡		x	x	x
Assessment Tools¶¶¶				
EQ-5D-5L score (Adults)	x	x	x	x
mMRC score (Adults)	x	x	x	x
GAD-7 score (Adults)	x	x	x	x
PHQ-9 score (Adults)	x	x	x	x
FSS score (Adults)	x	x	x	x

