ISI score (Adults)	x	x	x	x
EQ-5D-Y (Children 4–15 years)	x	x	x	x
PROMIS (Children 8–17 years)	x	x	x	x
SDQ score (Children 4–17 years)	x	x	x	x

°Baseline Assessment: Conducted at the time of hospitalization for COVID-19 at Gansu Provincial Hospital from 2022 to 2023.

°°Follow-Up Visits: Conducted via structured telephone interviews at three time points from 2024 to 2027.

Visit 1 (24 months post-discharge): PASC diagnosis.

Visit 2 (36 months post-discharge): Long-term outcome assessment.

Visit 3 (48 months post-discharge): Final long-term outcome assessment.

*Demographics: Includes age, gender, ethnicity, marital status (for adults), residential status during infection, education background, personal finances (for adults), work status (for adults), and BMI. These details are tailored to ensure age-appropriateness, with specific personal and professional information omitted for children.

†Environmental/socio-economic Factors: Encompasses sulfur dioxide (SO_2_), nitrogen dioxide (NO_2_), ozone (O_3_), particulate matter 10 (PM_10_), particulate matter 2.5 (PM_2.5_), Normalized Difference Vegetation Index (NDVI), temperature, precipitation, relative humidity, wind speed, per capita GDP, income levels, employment status, job types, education level, and living condition. This comprehensive data helps examine the environmental contexts affecting health outcomes.

‡Symptoms Monitoring: Tracks a wide array of symptoms across various systems.

Respiratory: Difficulty breathing, cough, chest pains.

Digestive: Abdominal pain, diarrhea, nausea, vomiting, loss of appetite, constipation.

Cardiovascular: Palpitations, tachycardia, bleeding.

Musculoskeletal: Arthralgia, myalgia, impaired functioning and mobility.

Nervous System: Headaches, dizziness, “brain fog,” sensory impairments, insomnia, and other sleep difficulties.

Other: Fever, fatigue, skin rashes, irregular menstrual cycles (in females over 12 years of age), erectile dysfunction (in males).

¶Lifestyle Factors: Includes smoking and drinking status, providing insights into behaviors that may influence disease progression and recovery.

**Vaccination Information: Documents the dose and timing of COVID-19 vaccinations, critical for assessing vaccine efficacy and patient immunity.

††Reinfection Data: Tracks instances of SARS-CoV-2 reinfection, including timing and test results (PCR, antigen, self-reported symptoms), to understand immunity and disease dynamics.

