‡‡Recovery Assessment: Includes a single question about recovery perception post-COVID-19, with responses categorized as yes, no, or unsure.

¶¶Comorbidities: Comprehensive data collection on conditions such as hypertension, various cardiovascular and respiratory diseases, diabetes, chronic liver and kidney diseases, metabolic disorders, nervous system diseases, psychiatric conditions, cancers, rheumatism, tuberculosis, and anemia, essential for assessing co-impact on health outcomes.

***Laboratory Test Results: Analysis of blood count, electrolytes, renal and liver functions, inflammatory markers, and coagulation profiles to provide a physiological snapshot of health impacts.

†††Treatment: Detailed record of all treatments administered, including medications, oxygen therapy, mechanical ventilation, ICU care, and other interventions, helping to correlate treatment strategies with outcomes.

‡‡‡Medical management: Information of visiting a doctor for any reason and treatment undertaken during follow-up.

¶¶¶Assessment Tools: Includes the 5-level EQ-5D version (EQ-5D-5L), The Modified Medical Research Council (mMRC) Dyspnea Scale, The Generalized Anxiety Disorder-7 (GAD-7), the Patient Health Questionnaire-9 (PHQ-9), The Fatigue Severity Scale (FSS), The Insomnia Severity Index (ISI), The EuroQol Five-Dimension Youth Questionnaire (EQ-5D-Y) assesses health-related quality of life, The Strengths and Difficulties Questionnaire (SDQ), The Patient-Reported Outcomes Measurement Information System (PROMIS).

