#### Secondary outcomes

The secondary outcomes of this study focus on assessments of the acute infection phase, its progression, the effectiveness of medical management strategies in shaping the trajectory of PASC (38). These assessments are conducted during the follow-up visits, designed to reassess the persistence or resolution of symptoms and evaluate changes in health status since the acute phase of the infection.

The evaluation includes documenting persisting symptoms and identifying any new clinical conditions diagnosed since the initial COVID-19 infection, as well as reviewing medical management strategies such as the reasons for doctor visits and treatments received during the follow-up period. Analysis objectives includes the persistence and progression of symptoms, with a specific focus on respiratory difficulties, overall quality of life, and mental health issues, including anxiety and depression (39). For pediatric populations, the assessment is tailored to specifically monitor the recovery of symptoms relevant to children and adolescents (40), addressing the unique challenges faced by these age groups in the aftermath of COVID-19.

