### Variables and data collection

#### Baseline variables

Individual baseline variables will be collected from the Gansu PASC dataset. We gather comprehensive health data during patients’ initial hospitalization for COVID-19. This baseline information serves as a reference to distinguish between pre-existing conditions and symptoms that may be attributed to PASC (41). These variables include demographic factors such as age, gender, ethnicity, marital status, educational background, employment status, and body mass index (BMI). Comorbidities recorded include hypertension, diabetes, respiratory diseases, liver diseases, and other relevant conditions. The Charlson Comorbidity Index (CCI) was adapted using a modified formula to assess morbidity and mortality risks. Conditions were scored as follows: one point for congestive heart failure, chronic pulmonary disease, diabetes, and other conditions; two points for chronic kidney disease and malignant neoplasms; three points for moderate to severe liver disease; and six points for Acquired Immunodeficiency Syndrome (AIDS) (42). Based on the CCI, comorbidities were categorized as mild (0–1), moderate (2–6), or severe (>6). Baseline laboratory assessments included complete blood counts, electrolyte panels, renal and liver function tests, inflammatory markers, and coagulation profiles. Initial treatment protocols involved various medications and supportive care measures, such as oxygen therapy, mechanical ventilation, and immunoglobulin treatments, with emergency interventions including tracheal intubation and cardiopulmonary resuscitation as required.

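### The protocol contradicts itself on when individual socioeconomic exposures are measured, and sets no time order between medical management and symptoms, so reverse causation is left open

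*Protocol article*

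**What the plan says.** **Socioeconomic items.** The Socioeconomic data section, which describes how these data are obtained, states that "income levels, employment status, job types, education level, and living conditions will be collected during follow-up visits", with the provincial yearbook as a further source. Under Follow-up assessments and in Table 1, the calls fall at 24, 36 and 48 months after discharge, and the 24-month call is the one that diagnoses PASC.

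Table 1 (Study population) has a row "Environmental/socio-economic factors" marked in the Baseline column and nowhere else. Its footnote lists "per capita GDP, income levels, employment status, job types, education level, and living condition", which are the same items. The Demographics row is also marked at baseline only and includes "education background, personal finances (for adults), work status (for adults), and BMI". Baseline variables names employment status and educational background among the items taken from the hospital dataset. Follow-up assessments then adds that demographic information is updated at the calls.

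**Medical management.** Table 1 marks this at Visits 1, 2 and 3, the same calls as symptoms, and not at baseline. Its footnote defines it as "Information of visiting a doctor for any reason and treatment undertaken during follow-up". Secondary outcomes includes "the effectiveness of medical management strategies in shaping the trajectory of PASC"; the Abstract calls the same objective efficacy.

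**Safeguards.** The causal inference section plans directed acyclic graphs, structural equation modelling, propensity score matching and sensitivity analyses. It states no rule that an exposure must be dated before the outcome. The limitations in the Discussion name selection bias and recall bias, not reverse causation.

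**The concern.** The study sets out to estimate how socioeconomic conditions influence the onset and course of PASC, and it uses causal language. That requires exposures dated before the outcome. Two years after infection, being out of work or on a lower income may be a result of PASC. If that status is entered as a risk factor, the model can return an association with the arrow reversed.

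Medical management has a related problem. People with worse symptoms see doctors more often, and the study itself recommends further evaluation according to symptoms reported on the call (Follow-up assessments). An analysis that sets care against symptoms from the same call can make useless or even helpful care look harmful. At stake are the socioeconomic aim and one named secondary objective.

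**Working it through.** The plan gives no figure on this point to reproduce. The check sets the places side by side and then sizes the possible bias on stated assumptions.

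**1. Timing of each item**

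| Item | Table 1 and footnotes | Text sections |
|---|---|---|
| Income, job type, living conditions | Baseline only | Follow-up visits (Socioeconomic data); not in the Baseline variables list |
| Employment | Baseline only | Baseline (Baseline variables) and follow-up visits (Socioeconomic data) |
| Education | Baseline only | Baseline and follow-up visits; largely fixed in adults |
| City-level figures | Baseline only | Yearbook; one patient's PASC cannot change them |
| Medical management | Visits 1–3 | Follow-up visits; no conflict |
| Symptoms | Baseline, Visits 1–3 | Follow-up visits; no conflict |

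The conflict therefore matters for income, employment, job type and living conditions. Study population says baseline data come from hospital records. For income, job type and living conditions, the only individual-level collection step that the text describes is the follow-up call. The Primary outcome section dates the first follow-up at 12 months rather than 24; that is a separate discrepancy, and either date is after infection.

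**2. Size of the bias if follow-up work status is the exposure**

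Assumptions, none from the documents: work status has no effect on PASC; 30% are not working before infection in both groups; 3% of workers without PASC, and a share q of workers with PASC, leave work before the call.

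- Not working at follow-up, no PASC: 0.30 + 0.70 × 0.03 = 0.321; odds 0.321/0.679 = 0.473.
- Not working at follow-up, PASC: p = 0.30 + 0.70 × q.
- Spurious odds ratio = [p/(1 − p)] / 0.473.

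| q | p | Odds | Odds ratio |
|---|---|---|---|
| 3% | 0.321 | 0.473 | 1.00 |
| 5% | 0.335 | 0.504 | 1.07 |
| 10% | 0.370 | 0.587 | 1.24 |
| 20% | 0.440 | 0.786 | 1.66 |

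With status dated before infection, the odds ratio is 1.00 by construction.

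**3. Chance that the spurious association reaches p < 0.05**

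Two-sided normal approximation: z = (p − 0.321)/SE, with SE = √[p(1 − p)/n₁ + 0.321 × 0.679/n₂]; the chance is about Φ(z − 1.96) + Φ(−z − 1.96).

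Example: 4,000 analysed, 30% with PASC assumed, q = 10%. Then n₁ = 1,200 and n₂ = 2,800, SE = 0.0165, z = 0.049/0.0165 = 2.97, and the chance is 84%. For q = 5% it is 14%; for q = 20%, about 100%.

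With 2,000 analysed and 10% with PASC (n₁ = 200, n₂ = 1,800), the chances are 7%, 28% and 90% for q = 5%, 10% and 20%.

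**4. Medical management, no true effect of care**

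Assume that 30% of patients without persistent symptoms see a doctor (odds 0.30/0.70 = 0.429), against 40%, 50% or 60% of those with them.

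- 40%: (0.40/0.60)/0.429 = 1.56
- 50%: (0.50/0.50)/0.429 = 2.33
- 60%: (0.60/0.40)/0.429 = 3.50

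These odds ratios of care with persistent symptoms arise from care-seeking alone.

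**The case against.** The strongest reply is that nothing shows a follow-up value entering any model as the exposure. Table 1 puts the same items at baseline, and if pre-infection values are used, reverse causation from PASC does not arise for them. The Socioeconomic data section says when a question is asked, not which period it covers; a call can ask about status at infection, and the Demographics footnote does refer to residential status during infection. The interview form is not shown. This stands: a reader might infer that the socioeconomic question cannot be answered, and the documents do not support that. What remains is that two places disagree and no sentence settles the value or its reference date.

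On management, the record covers treatment over the preceding interval, so recording it at the same call does not make it simultaneous with current symptoms. Much of the problem is confounding by indication, for which graphs and propensity scores are planned. Lag structure is often left to the analysis plan, and three visits make a lagged analysis possible. This stands in part. The objective is nevertheless worded as efficacy or effectiveness without any time order, and a propensity score does not determine direction when care and symptoms cover the same interval. A reader might also infer that management is bound to look harmful, or that matching will condition on consequences of PASC. The first is a risk, not a certainty; the second assumes a matching set that the article does not name.

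The size is wholly assumed. At a 5% exit rate the bias is small, and job exit matters less for the children and over-65s in the cohort.

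**Conclusion.** The point holds as a contradiction on timing that leaves reverse causation open, not as proof that the exposures follow the outcome. It concerns individual income, employment, job type and living conditions. Adult education and yearbook figures are largely outside it.

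If follow-up values are used as exposures for PASC, the spurious odds ratio for not working runs from 1.07 to 1.66 over the assumed exit rates of 5% to 20%, given 30% not working beforehand and 3% exit without PASC. If pre-infection values are used, it is nil.

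For management the timing is not in dispute. An unordered analysis of effectiveness could show odds ratios of 1.56 to 3.50 from care-seeking alone, on the assumed visit rates.

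The interview part needs settling before the calls are made: if only current status is asked and the hospital record lacks the item, no later model recovers pre-infection status.

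**What to change.** 1. Reconcile the Socioeconomic data section with Table 1 and its footnotes, item by item, separating individual items from yearbook figures.
2. Define individual socioeconomic exposures for PASC onset as status before the index admission, from the hospital record where present and otherwise asked at Visit 1 with that reference date.
3. Use follow-up values only as outcomes or as time-varying predictors of outcomes at later visits.
4. Relate management reported up to Visit k to the outcome at Visit k+1, adjusted for symptom severity at Visit k and acute severity.
5. Word the management objective as association in the Abstract and in Secondary outcomes.

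The cost is some reworded interview items and one lagged model. Some pre-admission values will be recalled about two years later. Visit 3 management cannot be related to a later outcome. Lagging removes simultaneity but not all confounding by indication, which should be stated as a limitation.

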### Assessment tools

To ensure a comprehensive and nuanced evaluation across different age groups, the study employs a range of validated assessment instruments. For more detailed descriptions of these tools, please refer to Supplementary Material 1.

#### For adults

(1) The 5-level EQ-5D version (EQ-5D-5L) (54) is used to evaluate health-related quality of life; (2) The Modified Medical Research Council (mMRC) Dyspnea Scale (55) is employed to assess respiratory symptoms; (3) The Generalized Anxiety Disorder-7 (GAD-7) (56) and the Patient Health Questionnaire-9 (PHQ-9) (57) are used for mental health screening; (4) The Fatigue Severity Scale (FSS) (58) is utilized to measure fatigue levels; and (5) The Insomnia Severity Index (ISI) (59, 60) is applied to assess sleep disturbances.

#### For children and adolescents

(1) The EuroQol Five-Dimension Youth Questionnaire (EQ-5D-Y) (61) assesses health-related quality of life; (2) The Strengths and Difficulties Questionnaire (SDQ) (62) evaluates behavioral and emotional health; and (3) The Patient-Reported Outcomes Measurement Information System (PROMIS) (63) is used to assess physical, emotional, and social health indicators.

### Statistical analysis

A variety of statistical methodologies will be employed to analyze the primary and secondary outcomes in this study. The data analysis begins with descriptive and inferential statistical methods to identify patterns and establish correlations. Continuous data will be presented as means with standard deviations (SD), while categorical variables will be reported as percentages. For comparisons across groups, analysis of variance (ANOVA) will be used for continuous variables, and chi-square tests for categorical variables, both with Bonferroni corrections applied in post-hoc analyses. A significance level of *p* < 0.05 will be consistently applied, with adjustments made for multiple comparisons to enhance the reliability of results. Logistic regression models will be employed to evaluate the impact of multiple factors on the severity of PASC. We will utilize a multivariable logistic regression model to analyze the relationship between various independent variables, including demographic factors, clinical characteristics, and environmental exposures, and the binary outcome of PASC presence or absence. The model will integrate variables selected based on clinical relevance and statistical significance derived from preliminary univariate analyses, ensuring that only factors significantly associated with the outcome are included in the final analysis. Variables for inclusion will be chosen based on their potential impact on PASC, informed by both clinical judgment and empirical evidence from initial analyses. We plan to investigate interaction terms, particularly between key demographic and clinical variables, to explore complex interactions that may affect PASC risk. Model fit will be assessed using the Hosmer-Lemeshow test for goodness-of-fit and Receiver Operating Characteristic curve analysis to evaluate predictive accuracy. We will also employ validation techniques such as split-sample validation or cross-validation to confirm the model’s robustness. Sensitivity analyses will be conducted to examine the stability of our results under various assumptions regarding data missingness and potential measurement errors, ensuring that our findings are reliable and applicable across different scenarios. Additionally, advanced analytical techniques will complement these methods, utilizing R (version 4.3.0) with the ‘gpboost’ and ‘stats’ packages and Python (version 3.10) with ‘sklearn’ and ‘gpboost.’

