**Methods and analysis:**

The study will enroll over 4,000 confirmed COVID-19 patients from Gansu Provincial Hospital, treated from December 2022 to May 2023, as the baseline. These patients are spread across 14 cities in Gansu Province, with geographic coordinates ranging from 92°13′E to 108°46′E and 32°31’N to 42°57’N. Follow-ups will be conducted via structured telephone interviews at 24, 36, and 48 months post-discharge, from 2024 to 2027, to assess PASC and long-term health outcomes. Participants will be categorized into three age groups: children and teenagers (birth to 18 years), adults (18–65 years), and the older adult (over 65 years). Environmental and socioeconomic data corresponding to each case are also integrated. The primary objective is to assess the persistence and long-term health outcomes of PASC symptoms. Secondary objectives focus on evaluating the acute infection phase, its progression, and the efficacy of medical management strategies in influencing PASC trajectories. Mixed-effects models will be utilized to evaluate the impact of various factors on PASC, while spatiotemporal analyses will explore the correlations between environmental and socioeconomic conditions and the diagnosis and recovery trajectories of PASC.

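### Post-hoc pairwise tests use single-step Bonferroni. Holm's procedure keeps the same 5% family-wise bound and can show more second and third differences where three or more groups are compared

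*Protocol article*

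**What the plan says.** The Statistical analysis section opens with descriptive and inferential comparisons: "For comparisons across groups, analysis of variance (ANOVA) will be used for continuous variables", with chi-square tests for categorical variables, "both with Bonferroni corrections applied in post-hoc analyses". It adds that "A significance level of *p* < 0.05 will be consistently applied", "with adjustments made for multiple comparisons to enhance the reliability of results". The section does not name the groups or the number of comparisons.

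The Abstract says that "Participants will be categorized into three age groups" (children and teenagers, adults, older adults). Table 1 limits the questionnaire scales by age: EQ-5D-5L, mMRC, GAD-7, PHQ-9, FSS and ISI are for adults, and EQ-5D-Y, PROMIS and SDQ are for children. Symptoms (apart from two sex-specific items), reinfection, perceived recovery and laboratory results carry no such limit, and PASC status is assessed in the whole cohort.

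**The concern.** Single-step Bonferroni tests every one of m pairwise p-values at 0.05/m. Holm orders the p-values and tests the smallest at 0.05/m, the next at 0.05/(m − 1), and so on, stopping at the first failure. Both bound the family-wise error at 5% under any dependence between the tests. Holm's thresholds are never stricter, so it cannot reject less.

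The choice matters only once a first difference has been found. Which further pairs of groups differ is then judged against a stricter threshold than the error bound requires. The Discussion presents age-specific recovery patterns as a strength of the long follow-up, and describing such patterns needs more than one pairwise contrast. A three-group comparison could also arise elsewhere, for example across the mild, moderate and severe comorbidity categories.

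**Working it through.** **No figure to reproduce.** The article gives no power, effect size or derived sample size for these comparisons.

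**Inputs from the article.** Level 0.05 (taken as two-sided, since sidedness is not stated); Bonferroni for post-hoc tests; three age groups, hence 3 pairs if these are the groups compared; a cohort that "will enroll over 4000 individuals".

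**Assumed inputs.** Age split 300/2,200/1,500 (total 4,000); SD 1; equally spaced means 0, d, 2d; pairwise z-tests with known variance.

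**Thresholds for 3 pairs.**
- Bonferroni: 0.05/3 = 0.0167 for each pair. Sum 3 × 0.0167 = 0.05.
- Holm: 0.05/3 = 0.0167, then 0.05/2 = 0.025, then 0.05.
- The first step is identical, so the two methods always agree on whether anything is rejected.

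**Hand check at d = 0.10 under Bonferroni.** The standard error of a difference is √(1/n₁ + 1/n₂), and the two-sided 0.0167 critical value is 2.394. Power is approximately Φ(difference/SE − 2.394).
- 300 v 2,200: SE 0.0616, 0.10/0.0616 = 1.62, power 22%.
- 300 v 1,500: SE 0.0632, 0.20/0.0632 = 3.16, power 78%.
- 2,200 v 1,500: SE 0.0335, 0.10/0.0335 = 2.99, power 72%.
- Average: (22 + 78 + 72)/3 = 57%, which agrees with the simulated value below.

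**Simulation (400,000 replicates).**

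| Spacing d (SD) | At least one difference, either method | All three, Bonferroni | All three, Holm | Average pairwise power, Bonferroni | Average pairwise power, Holm |
|---|---|---|---|---|---|
| 0.05 | 33% | 0.5% | 2% | 15% | 17% |
| 0.10 | 91% | 14% | 28% | 57% | 64% |
| 0.12 | 98% | 27% | 45–46% | 71% | 78% |
| 0.20 | 100% | 80% | 90% | 93% | 97% |
| 0.30 | 100% | 99.4% | 99.8% | 99.8% | 99.9% |

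**Fewer patients followed up.** If half the cohort is reached (150/1,100/750), the chance of showing all three differences at d = 0.20 is 44% with Bonferroni and 62% with Holm.

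**Error rates (300/2,200/1,500).**
- All means equal: family-wise error 4.1% under both methods.
- Means 0/0.3/0.3, so that one null is true beside two real differences: the false-positive rate on that null is 1.7% with Bonferroni and 5.0% with Holm.

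**Where nothing changes.** On the adult-only scales, of the three age groups only the 18–65 and over-65 groups can be compared. That is one pair, tested at 0.05 under either method.

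**The case against.** The strongest reply is that nothing in the plan is wrong. Bonferroni is prespecified, holds the error rate it is meant to hold, and fits the stated aim of reliable results; preferring Holm is a choice between valid methods. That stands, and it is why this is an optional improvement and not an error.

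Four further points also stand:
- The link to the age groups is an inference. The analysis section speaks only of groups, and no aim asks for a full ordering of the three age groups. Still, post-hoc testing after ANOVA implies at least three groups, and the age groups are a natural candidate.
- The calculation is for a continuous outcome. Several outcomes shared by all ages are categorical, for which no power was computed. Holm's ordering over Bonferroni holds for any set of valid p-values, but the percentages do not transfer.
- The gain is large only for small effects, here around 0.10 to 0.20 SD, or for smaller numbers followed up.
- These tests are the opening step. Risk-factor effects come from the logistic, GLMM, GPBoost and causal models, which the correction does not touch.

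A reader might go further and infer that real differences between age groups are being missed for nothing in return. The article does not support that. Whether any difference is missed depends on group sizes and effects it does not state. Bonferroni also gives something back: simple matching simultaneous intervals and a lower error rate on a remaining true null.

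**Conclusion.** The point holds as a minor, nearly free gain in power. For three or more groups, Holm keeps the 5% family-wise bound under the same assumptions and never rejects less than Bonferroni, so second and third real differences may be missed under the present wording. That ordering does not depend on any assumption about the data. The size does: under the assumed 300/2,200/1,500 split with SD 1 and equal spacing, the gain in the chance of showing all three differences runs from about 1.6 points at 0.05 SD (2.1 − 0.5), through about 15 points at 0.10 and 10 at 0.20, to 0.4 points at 0.30. It does not amount to a defect in the plan, and no conclusion from the main models depends on it.

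**What to change.** In the Statistical analysis section, replace the Bonferroni wording for post-hoc pairwise tests by *Holm-adjusted p-values*, for both the ANOVA and the chi-square follow-up comparisons.

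The cost is one phrase, with no new data and no higher family-wise bound. There are two small downsides. Simultaneous confidence intervals, if shown, would stay Bonferroni-based and may occasionally disagree with the Holm p-values; a sentence saying so is enough. The error rate on a true null that remains beside real differences rises from about 1.7% to at most 5%, which is within the bound already planned.
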